## 2. Materials and Methods

### 2.1. Study Design and Setting

This study is an assessor-blinded, multicenter trial with a ten-week treatment period followed by a two-month follow-up. It follows the consensus-based core recommendations from the stroke recovery and rehabilitation expert group [18], thereby improving the study’s development and the SPIRIT statement [30]. This study has been approved by the Research Ethics Committee of the Institut d’Investigació en Atenció Primària Jordi Gol (IDIAP Jordi Gol) (num. 24/190-P). It has been registered at ClinicalTrials.gov (NCT06944197). Participants will be randomly allocated in a 1:1:1 ratio to the control group (CG) (*n* = 25) or the experimental groups (EG1) (*n* = 25); (EG2) (*n* = 25). Patients are being recruited by five primary care centers of the Southern Metropolitan Management of the Institut Català de la Salut (ICS) in Catalonia, Spain.

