### 2.2. Recruitment and Blinding

Participants will be randomly assigned to one of the three intervention groups using a computer-generated sequence through Random.org. To ensure allocation concealment, only the principal investigator (PI) will have access to the randomization list. This allocation will take place after obtaining informed consent, but before baseline assessments (T0), and the allocation will not be disclosed to the physiotherapists or outcome assessors until the participant has been formally enrolled in the study.

Although no stratification or block randomization procedures were applied, rigorous measures have been implemented to minimize potential bias and ensure the internal validity of the study. Outcome assessments will be performed by independent, previously trained physiotherapists acting as blinded assessors. In addition, statistical analyses will be conducted by researchers blinded to group allocation, thereby strengthening the objectivity of the results. All data will be recorded in a secure digital system, password-protected and accessible only to authorized members of the research team.

Prior to the randomization process, participant recruitment will follow a series of steps designed to ensure ethical transparency and informed understanding. First, the principal investigator, together with the physiotherapist responsible for each assigned center, will provide detailed information to collaborating healthcare professionals regarding the inclusion and exclusion criteria, as well as the general characteristics of the study. Second, physiotherapists from the research team will contact potential participants by phone through their primary care center to explain the purpose, design, duration, and potential risks and benefits of the study. If a patient expresses interest, a face-to-face appointment will be scheduled to provide more detailed information and resolve any questions. Informed consent will be obtained during this appointment, prior to accessing the participant’s medical history, in compliance with ethical standards and data privacy regulations.

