After group allocation and before starting treatment (T0), pre-intervention tests will be conducted to assess the baseline values of the primary and secondary outcome measures. A maximum of one week after completion of the intervention (T1), data will be collected for all efficacy outcomes (see Section 2.5). The same data will be collected two months after the end of the intervention (T2) (Figure 1). During the ten weeks of intervention, data will be collected in each session regarding adherence to the intervention (number of sessions and duration), intensity, exercises performed by each patient, and any incidents. All visits and efficacy evaluations will be conducted at the patient’s reference primary care center with the corresponding evaluating physiotherapist.

The study uses a single-blind design due to the nature of the interventions; therapists and participants cannot be blinded to treatment allocation. To avoid detection bias, efficacy outcomes will be assessed by an independent, blinded evaluator. Each center has a trained physiotherapist assessor, supervised by the principal investigator. The training information is available online and in paper format. Additionally, all statistical analyses will be conducted by researchers blinded to group allocation.

All data will be recorded in an online document shared by all the evaluators of the research team. A form created in a spreadsheet will be used. All researchers are trained in the use of the scales and the document, and they have a help guide, as well as a consultation service directly with the principal investigator of the study who is responsible for the logistics of the study. Access to the study registration document is restricted to authorized study personnel via password.

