### 2.3. Sample Size

The sample size was calculated using an a priori power analysis conducted with G*Power software (version 3.1.9.7). The calculaion was based on a mixed-design repeated-measures ANOVA with one between-subjects factor (three groups) and one within-subjects factor (three time points). A conservative medium effect size (f = 0.32) was selected for the calculation, which represents a smaller effect than that reported by Aphiphaksakul et al. [31], who reported functional improvements following a mobili-application-based training protocol in stroke patients. This effect size corresponds to an expected between-group difference of approximately 8–10 points on the Barthel Index, substantially exceeding the established MCID of 1.85 [32,33], thereby ensuring clinically meaningful differences. The analysis employed a significance level of α = 0.05 and a statistical power of 0.80 (1 − β = 0.80), and 10% dropout rate. Based on these parameters, the required sample size was determined to be 75 participants, with 25 participants allocated to each group.

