### 2.6. Interventions

#### Intervention Description

The sample will be randomized systematically and pseudonymized. The 75 subjects will be divided into three intervention groups, and a different intervention will be carried out in each of them:

-Guidance Document Group (*n* = 25): The primary and community care physiotherapist will carry out an individual face-to-face consultation at the Primary Care Center with the person participating in the study, where they will deliver a guide document for the management of the pathology, as well as guidelines for the promotion and prevention of important health issues after a stroke. The document is the “Guide aimed at people affected by cerebral vascular disease and their families and caregivers” created by the Department of Health of the Generalitat de Catalunya, together with the Stroke Foundation in 2022. This group is the control, since the intervention is the one that most resembles the intervention that is currently being carried out in Catalonia from the Primary Care Centers for Stroke in the chronic phase.

No additional therapeutic contacts are scheduled after this initial session, and no monitoring is performed, as this reflects current standard practice in Catalonia.

No adherence tracking applies in this group, as no structured exercise program is prescribed.

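### Randomization without blocks or strata does not guarantee the stated 25 per arm and leaves arms unbalanced across five centres, each with its own assessor, and the stated model has no centre term

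*Protocol article*

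**What the plan says.** Section 2.2 says that allocation is made "using a computer-generated sequence through Random.org" and then adds: "Although no stratification or block randomization procedures were applied". In place of these it offers blinded assessors, blinded analysts and secure data handling.

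Arm sizes are nevertheless given as definite numbers. Section 2.1 states a 1:1:1 ratio with 25 in each arm, Section 2.3 says "the required sample size was determined to be 75 participants, with 25 participants allocated to each group", and Section 2.6 repeats 25 for each group. Section 2.6 also describes the method in other words: "The sample will be randomized systematically and pseudonymized".

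On centres, Section 2.1 says "Patients are being recruited by five primary care centers". Section 2.2 says "Each center has a trained physiotherapist assessor, supervised by the principal investigator", and also: "All visits and efficacy evaluations will be conducted at the patient’s reference primary care center with the corresponding evaluating physiotherapist".

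The model in Section 2.8 is a 3 × 3 mixed ANOVA with time, group and their interaction. Centre is not among its terms.

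**The concern.** There are two linked problems.

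1. **Arm sizes.** A sequence with neither blocks nor strata does not by itself produce 25/25/25. Either the totals were fixed in some way that the article does not describe, or 25 per arm is an expected number presented as a certain one. The description in Section 2.6 does not settle which, because systematic allocation is not defined and does not sit easily with a random computer list.
2. **Centre balance.** Every patient is assessed at the home centre by that centre's assessor, so centre carries both case-mix and rater differences. Nothing in the allocation balances arms within centres, and nothing in the stated model adjusts for centre. The safeguards listed in Section 2.2 deal with detection bias and data security. They affect neither arm size nor centre balance.

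At stake are some precision and the credibility of the one realised comparison. With about 15 patients per centre, a chance shortage of one arm at a centre with a lenient or strict assessor would pass into the arm contrast unadjusted.

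**Working it through.** **Inputs.** From the article: N = 75, three arms at 1:1:1, five centres, f = 0.32, α = 0.05, power 0.80, dropout 10%. Assumed: 15 patients per centre (75/5; the split is not given), allocation unrestricted unless noted, and equally spaced arm means for the power check.

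**The plan's own sample size.** One route reproduces it: the between-groups test of a repeated-measures ANOVA with three times and an assumed correlation of 0.5. The noncentrality is λ = N f² m / [1 + (m − 1)ρ]. At N = 66, λ = 66 × 0.1024 × 3 / 2 = 10.1, and power is 0.801. Then 66 / 0.9 = 73.3, so 74, which becomes 75 for three equal arms. The stated total is therefore reachable. The question here is how it divides.

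**Arm sizes under unrestricted allocation.**
- P(25/25/25) = 75! / (25!)³ / 3⁷⁵ = 0.0109.
- SD of one arm's size = √(75 × 1/3 × 2/3) = 4.1; 95% range 17 to 33.
- Simulation (1,000,000 draws): median gap between largest and smallest arm 8; P(gap ≥ 10) = 0.37; P(smallest arm ≤ 20) = 0.39.

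A single shuffled list with 25 entries per arm gives 25/25/25 with certainty.

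**Power cost of unequal arms.** For equally spaced means, d = f√6 = 0.32 × 2.449 = 0.78 between the extreme arms. Power ≈ Φ(d / √(1/n₁ + 1/n₂) − 1.96), with no multiplicity adjustment or dropout.

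| Arms compared | Power |
|---|---|
| 25 v 25 | 79.1% |
| 20 v 30 | 77.5% |
| 17 v 33 | 74.7% |

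The variance of a pairwise contrast rises by 2.9% on average and by 20% at the 95th percentile.

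**Balance within centres (15 each).** Under unrestricted allocation, P(a given centre splits 5/5/5) = 15! / (5!)³ / 3¹⁵ = 756,756 / 14,348,907 = 0.053. All five doing so has probability 0.053⁵, effectively zero.

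| | Unrestricted (100,000 draws) | One list, totals fixed at 25 (20,000 draws) |
|---|---|---|
| Some centre has an arm ≤ 2 | 74% | 58% |
| Some centre has an arm ≤ 1 | 26% | 15% |

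Fixing the overall totals therefore reduces the centre problem but does not remove it.

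**How a centre difference reaches the result.** Let b_c be the offset of centre c. The contrast between arms A and B at one visit picks up Σ_c (share of A from c − share of B from c) × b_c. With 25 per arm, each patient of imbalance at a centre passes 1/25 = 4% of that centre's offset into the contrast. If b_c is the same at T0, T1 and T2, it drops out of every within-patient change and so out of the group-by-time interaction. Adding arbitrary constant centre offsets to simulated 3 × 3 data left the interaction F at 2.0167. What remains is the between-group effect, single-visit contrasts, and offsets that change over time, such as assessor drift or centre-specific change.

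**What stratified blocks would do.** Varying blocks of 3, 6 and 9 within centre bring the mean gap between largest and smallest arm to about 2, and gaps of 10 or more essentially vanish. They give exactly 25/25/25 in only about 12–20% of simulated trials, because last blocks stay incomplete.

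**The case against.** The strongest reply is that the article never calls the method simple or unrestricted. One shuffled list with 25 entries per arm has no blocks or strata in the usual sense and delivers the stated numbers. This stands. A reader might infer that 25 per arm cannot be reached, but the text does not support that, and even unrestricted allocation has a 1.1% chance. What survives is that the article does not say how 25 is reached, and that fixed totals still leave centres unbalanced.

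A reader might also infer that the comparison is biased. It is not, in expectation: chance imbalance between centres costs precision only. Nor do assessor offsets that stay constant disturb the group-by-time test, provided that the same assessor sees the patient at each visit. Both replies stand.

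A third inference is that fixed totals would make late allocations predictable to the principal investigator. This adds nothing: as sole holder of the list, that person already sees every allocation.

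Finally, a centre covariate can be left to an analysis plan that is not at hand, and leaving out stratification is an openly declared choice. That is fair as far as it goes. But Section 2.8 names the terms of its model, and centre is not one of them. If the analysis plan already includes centre, that part of the point is met.

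**Conclusion.** The point holds in a limited form and is worth acting on, but it does not threaten the trial's validity. The stated method does not guarantee the stated arm sizes. On the assumption of unrestricted allocation, a gap of 10 or more between arms has a 37% chance, but the resulting power loss is only about 2 to 4 points at d = 0.78. A claim of serious power loss from unequal arms would not be supported.

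The larger part is centre. With 15 patients per centre assumed, some centre has an arm of two or fewer in 58% to 74% of trials, depending on whether totals are fixed, and the stated model does not adjust for it. The harm is lost precision and chance contamination of between-arm contrasts. How much precision is lost depends on the share of Barthel variance due to centre, which the article does not give. If it were 5–10% (an assumption), adjustment would remove about that share of error from between-arm contrasts, and none from the interaction unless centre differences change over time.

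**What to change.** 1. For participants not yet randomized, use computer-generated permuted blocks of varying size (for example 3, 6 and 9), stratified by centre, with block sizes undisclosed to the centres.
2. For all participants, add centre and centre-by-time to the model, or centre to the between-arm contrasts at T1 and T2. Centre alone would not help the interaction test.
3. State how the existing list was made and whether its totals were fixed. If they were not, describe 25 per arm as a target. Report actual arm sizes overall and by centre.
4. Replace the wording on systematic randomization in Section 2.6 with that description.

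Cost: a short amendment and a new list, with no extra patients. Centre uses 4 degrees of freedom (between-patient error 75 − 3 = 72 falls to 68), and centre-by-time uses 4 × 2 = 8 (within-patient error 72 × 2 = 144 falls to 136). Recruitment is under way, so the trial would contain two allocation schemes; the scheme used should be recorded for each participant. Small blocks at a site with unblinded therapists are slightly predictable, which is why sizes should vary and stay concealed. If changing the list is judged impractical, items 2 to 4 still stand alone.

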### 2.3. Sample Size

The sample size was calculated using an a priori power analysis conducted with G*Power software (version 3.1.9.7). The calculaion was based on a mixed-design repeated-measures ANOVA with one between-subjects factor (three groups) and one within-subjects factor (three time points). A conservative medium effect size (f = 0.32) was selected for the calculation, which represents a smaller effect than that reported by Aphiphaksakul et al. [31], who reported functional improvements following a mobili-application-based training protocol in stroke patients. This effect size corresponds to an expected between-group difference of approximately 8–10 points on the Barthel Index, substantially exceeding the established MCID of 1.85 [32,33], thereby ensuring clinically meaningful differences. The analysis employed a significance level of α = 0.05 and a statistical power of 0.80 (1 − β = 0.80), and 10% dropout rate. Based on these parameters, the required sample size was determined to be 75 participants, with 25 participants allocated to each group.

### 2.4. Selection Criteria

Patients will have to meet the following eligibility criteria to be included in the study. Inclusion criteria include being 18 years of age or older, having a medical diagnosis of stroke, and having had the condition for more than 6 months. Participants must have physical sequelae secondary to stroke, with a minimum score of 1 on the Medical Research Council scale for overall muscle strength of affected limbs, a maximum score of 3 on the Modified Ashworth scale for overall muscle tone of affected limbs, and a maximum score of 4 on the Modified Rankin scale for disability. Additionally, participants should have access to computer equipment, such as a tablet, desktop or laptop computer, or smartphone.

Exclusion criteria include undergoing other non-pharmacological physical treatments for the improvement and/or maintenance of stroke sequelae, previous decreased motor functional capacity with a Barthel scale score of less than 60 points, and cognitive and/or language barriers that hinder the correct understanding of the informed consent and intervention. Additionally, participation in another clinical trial during this study period that may impact the results of the variables to be evaluated is also an exclusion criterion.

During the study, participants may continue their usual daily physical activity (e.g., walking or household activities), but they may not engage in any additional structured physiotherapy, private rehabilitation, or therapeutic group sessions, as these could influence the study outcomes. To monitor possible concomitant therapies, participants will complete a weekly activity log, and the research physiotherapists will verify this information during each follow-up contact.

### 2.5. Outcome Measure

Descriptive data of the sample will be recorded, as well as anthropometric data and various assessment measures for the following evaluation variables.

The primary outcome is the degree of dependence or functional capacity for activities of daily living, which is assessed using the Barthel Index [32], and it is the validated scale used for the sample calculation [31].

The secondary outcomes have been classified into two categories: (1) Key Secondary Outcomes, which include motor function, muscle tone, muscle strength, balance, and quality of life, and (2) Additional Secondary Outcomes, which include gait performance (gait pattern and gait speed), perceived pain, fatigue, fall risk, subjectively perceived change after treatment, and adherence to the exercise program.

The secondary variables and their respective evaluation tools are as follows: motor function will be assessed using the Modified Motor Assessment Scale; muscle tone of the affected limbs will be measured with the Modified Ashworth Scale; muscle strength of the affected limbs will be evaluated using the Medical Research Council scale; balance will be assessed with the Postural Assessment Scale for Stroke Patients; walking efficiency will be measured using the Wisconsin Gait Scale and the 4 Meter Gait Speed Test; perception of osteomuscular pain will be evaluated through the Brief Pain Inventory; perception of fatigue will be measured using the Fatigue Severity Scale; fall risk will be assessed with the Time Up and Go Test; quality of life perception will be evaluated using the Newcastle Stroke-Specific Quality of Life Measure (Spanish version); and perception of subjective change post-treatment will be measured with the Global Rating of Change Scale (Table 1).

Adherence, included as an Additional Secondary Outcome, will be quantified as the proportion of prescribed sessions completed, the weekly frequency achieved, and the duration of each session, allowing further analysis of its potential influence on the functional outcomes observed across the intervention groups.

Although this broad set of outcomes aims to provide a comprehensive clinical profile of participants, the assessment burden is minimized through efficient scheduling of evaluation visits, grouping compatible measures within the same session, and using validated instruments with short administration times.

Given the number of secondary outcomes, results will be interpreted cautiously, and multiplicity will be addressed using appropriate statistical adjustments, as detailed in Section 2.8.

#### Assessments

The Barthel Index is a well-established and widely used tool for assessing physical disability, particularly in stroke patients. It consists of 10 items that evaluate personal care and mobility, yielding a total score ranging from 0 (totally dependent) to 100 (independent) [33].

The Modified Motor Assessment Scale (MMAS) is a valid and reliable instrument used to assess motor function in stroke patients, focusing on limb and trunk mobility. Scoring ranges from 0 to 5 for each item, with higher scores indicating better function. This tool demonstrates high interobserver and test–retest reliability, along with strong construct and concurrent validity [34,35].

The Modified Ashworth Scale (MAS) is widely used for assessing muscle tone and spasticity in stroke patients. It scores spasticity from 0 (no spasticity) to 4 (severe spasticity). Its construct and concurrent validity are strong, confirming its utility in evaluating muscle tone and spasticity [36,37].

The Medical Research Council (MRC) Scale is a well-regarded tool for assessing muscle strength in stroke patients, scoring from 0 (no muscle contraction) to 5 (normal strength against gravity). The scale demonstrates good interobserver and test–retest reliability, along with solid construct and concurrent validity [38,39,40].

The Postural Assessment Scale for Stroke Patients (PASS) evaluates postural control and balance, focusing on a patient’s ability to maintain specific postures. It consists of 12 items, each scored from 0 to 3, where higher scores indicate better postural control. The PASS exhibits high reliability and predictive validity [41].

The Wisconsin Gait Scale (WGS) is a comprehensive tool for assessing gait, including postural control, stride length, and gait symmetry. It is scored from 0 to 3, with higher scores reflecting better gait function. The WGS has high interobserver and test–retest reliability, along with strong concurrent and predictive validity [31].

The 4-Meter Gait Speed Test assesses walking speed, a crucial measure of mobility, independence, and fall risk. The test is highly reliable for evaluating functional prognosis and rehabilitation progress [42].

The Brief Pain Inventory (BPI) measures pain intensity and its impact on quality of life, using a scale from 0 (no pain) to 10 (worst pain imaginable). The BPI is widely used due to its strong reliability and validity [43].

The Fatigue Severity Scale (FSS) evaluates the severity of fatigue and its impact on daily activities, with scores ranging from 1 (strongly disagree) to 7 (strongly agree). The FSS is highly reliable for monitoring fatigue in stroke rehabilitation [44].

The Timed Up and Go (TUG) Test assesses fall risk by timing how long it takes for a patient to stand up from a chair, walk 3 m, turn, return, and sit down. The TUG test is a reliable and valid measure for fall risk [45].

The Newcastle Stroke-Specific Quality of Life Measure (NEWSQOL) evaluates stroke-specific quality of life, encompassing physical, emotional, social, and cognitive domains. It has demonstrated high internal reliability and strong construct, concurrent, and predictive validity [46].

The Global Rating of Change Scale (GROC) measures the patient’s perception of changes in their health or functioning after an intervention. It demonstrates strong test–retest reliability and robust concurrent and construct validity [47].

Information regarding stroke diagnosis, medical history, and stroke onset will be collected from patient records in the ECAP programs (ICS). Additionally, data on participant characteristics, including sex, age, family support, primary caregiver involvement, medication use, comorbidities, dysphagia, lesion location and side, time post-stroke, and stroke severity (assessed by the NIHSS and modified Rankin Scale), will be gathered for comprehensive analysis.

